### Interventions

In the PNB group, bilateral PNB with 30 ml of 0.33 % ropivacaine (15 ml for each side) will be performed after the operation is finished. In the tramadol group, intravenous tramadol 1.5 mg/kg will be administered after the operation is finished.

### Outcome measures

All patients will be extubated after completion of the operation and then transferred to the PACU for outcome evaluation. Patients will be asked directly and observed by staff responsible for follow-up who were blinded to the group assignments for outcomes at 0, 0.5, 1, 2, 4, and 6 h after patient arrival in the PACU and after extraction of the urinary catheter. A questionnaire designed to collect the outcome data is shown in Table 1.

**Table 1 Tab1:**
[figure not shown]
Questionnaire for pudendal nerve block trial outcome evaluation

### Primary outcome

The primary outcome is the incidence of postoperative CRBD.

### Secondary outcomes

The following are the secondary outcomes of interest in the trial:The most important secondary outcome is the severity of postoperative CRBD, which will be assessed with a 4-point scale as follows: 0 = no CRBD; 1 = mild CRBD, existing only upon asking about it; 2 = moderate CRBD, stated by the patient spontaneously; and 3 = severe CRBD, demonstrated by behavioral response such as strong vocal responses or attempting to pull out the catheter [2]. When the severity of CRBD is evaluated as 2 or 3, the patient will be administered intravenous tramadol 1.5 mg/kg as a rescue treatment for bladder discomfort reduction [6], and postoperative tramadol requirement will be recorded and compared.Postoperative pain will be evaluated by the patients themselves using a single 11-point Numeric Rating Scale (NRS), which ranges from 0 to 10, where 0 indicates “no pain” and 10 represents “worst imaginable pain” [17]. If the patient complains about pain with an NRS score greater than 4, intravenous sufentanil 5 μg will be administered as a rescue analgesic treatment, and postoperative sufentanil requirement will be recorded and compared.Postoperative side effects will be recorded and analyzed. These include postoperative nausea/vomiting, sedation, dizziness, and dry mouth. Sedation will be assessed using the Ramsay Sedation Scale (1 = anxious, agitated, or restless; 2 = cooperative, oriented, and tranquil; 3 = responds to command, asleep; 4 = brisk response to light glabellar tap or loud noise; 5 = a sluggish response to light glabellar tap or loud noise; and 6 = no response) [18]. Patients with a Ramsay Sedation Scale score greater than 4 will be considered sedated.Acceptance of the indwelling urinary catheter will be evaluated by using an NRS score ranging from 0 (totally not acceptable) to 10 (totally acceptable) after extraction of the catheter.The incidence of complications related to PNB, including hemorrhage and/or hematoma, infection of injection site, and accidental systemic administration of ropivacaine, which will be recorded and evaluated for overall safety of this technique, will be recorded.

### Statistical analysis

An intention-to-treat analysis will be performed to compare all primary and secondary outcomes with the use of SPSS version 18.0 software (SPSS, Inc., Chicago, IL, USA). Demographic data will be compared using Student’s *t* test. The incidence of CRBD and postoperative side effects will be analyzed by chi-square test. The severity of CRBD will be analyzed using Fisher’s exact test. NRS scores for postoperative pain and acceptance of the indwelling urinary catheter will be analyzed using the Mann-Whitney *U* test. Postoperative tramadol and sufentanil requirements will be analyzed using the *Z* test. *p* < 0.05 will be considered to be statistically significant.

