### Sample size calculation

The incidence of CRBD has been reported to range from 47 % to 90 % according to different types of surgery, and male sex has been identified to be an independent predictor in previous studies [1, 3]. We investigated 367 male patients in the PACU of the Department of Anesthesiology, West China Hospital, from 21 June 21 to 17 July 2015 and found that 56.1 % (206 of 367) of them complained of CRBD. On the basis of this information, a difference of 25 % (e.g., 30 % vs. 55 %) in the incidence of CRBD values between two treatment groups is considered to be clinically important. The sample size was calculated to compare two proportions with two-sample noninferiority or superiority; assuming the difference between two groups at a 5 % significance level and a power of 0.80, 37 patients in each group are required for a comparison within the groups. Considering an estimated 20 % dropout rate, 47 patients in each group, and 94 patients in total, are required in this study.

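### The most important secondary outcome is an ordered 0-3 severity grade, but its stated test, Fisher's exact test, ignores the order; an ordinal test fits the question better and is usually more efficient

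*Protocol article*

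**What the plan says.** Under Secondary outcomes, the protocol article states: "The most important secondary outcome is the severity of postoperative CRBD, which will be assessed with a 4-point scale". The four points run from no CRBD through mild and moderate to severe, so each grade is worse than the one before.

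Under Statistical analysis, the test for this outcome is fixed: "The severity of CRBD will be analyzed using Fisher’s exact test". The text does not say that the grades will be collapsed into two groups. The same paragraph treats the other ordered scores differently: "NRS scores for postoperative pain and acceptance of the indwelling urinary catheter will be analyzed using the Mann-Whitney" U test. The threshold is p "< 0.05 will be considered to be statistically significant".

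The only effect size is for the primary outcome. Under Sample size calculation it is "a difference of 25 % (e.g., 30 % vs. 55 %) in the incidence of CRBD values". The article gives no severity distribution and no power for severity.

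**The concern.** The Design section frames the trial as a superiority test of pudendal nerve block (PNB) against tramadol. The natural severity question is therefore whether grades are lower with PNB. Applied to four grades, Fisher's exact test (Freeman-Halton form) asks only whether the two distributions differ in any way, and its p-value does not change if the grade labels are shuffled. The plan thus uses the ordering for lower-ranked outcomes and drops it for the one ranked highest among the secondaries.

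What is at stake is a real and consistent reduction in severity that goes undetected because the test spends power on patterns with no ordering. This is a method the article states, not a detail left to an unseen analysis plan.

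**Working it through.** **Figure to reproduce.** There is none, because the article states no power for severity. The group sizes used are the article's 37 evaluable and 47 enrolled per group (37/(1 − 0.20) = 46.25, rounded up to 47). The 37 itself does not follow from 55% vs 30% by the usual formulas: the pooled formula gives 61 per group two-sided and 48 one-sided. That is a separate matter and does not bear on the comparison of tests.

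**Inputs**
- From the article: P(grade 0) = 0.45 (tramadol) and 0.70 (PNB), from 55% vs 30% incidence; threshold 0.05; 37 and 47 per arm.
- Assumed: the split of grades 1 to 3 in the control arm, the pattern of the shift, and two-sided testing.

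**Two patterns of consistent benefit**
1. Proportional odds. The common odds ratio is (0.70/0.30)/(0.45/0.55) = 2.85. For control grades 45/25/20/10%, the cumulative odds 0.70/0.30 and 0.90/0.10 multiplied by 2.85 give cumulative probabilities 0.869 and 0.963. The PNB grades are then about 70.0/16.9/9.3/3.8%.
2. Severity mix among sufferers unchanged. Grades 1 to 3 are each multiplied by 30/55. The same control split gives 70.0/13.6/10.9/5.5%.

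**Simulated power, Fisher (exact, 2×4) / Mann-Whitney (tie-corrected), %**

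| Control grades 0/1/2/3 (%) | Pattern | 37 per arm | 47 per arm |
|---|---|---|---|
| 45/20/20/15 | Proportional odds | 44.9 / 61.8 | 56.5 / 72.8 |
| 45/25/20/10 | Proportional odds | 45.1 / 62.2 | 56.2 / 73.4 |
| 45/30/17/8 | Proportional odds | 45.0 / 60.8 | 56.1 / 73.0 |
| 45/35/15/5 | Proportional odds | 46.8 / 62.4 | 57.8 / 72.6 |
| 45/20/20/15 | Mix unchanged | 43.6 / 53.9 | 51.9 / 66.3 |
| 45/25/20/10 | Mix unchanged | 40.8 / 55.1 | 53.3 / 66.5 |
| 45/30/17/8 | Mix unchanged | 43.4 / 55.7 | 54.3 / 67.5 |
| 45/35/15/5 | Mix unchanged | 45.2 / 55.1 | 55.2 / 67.3 |

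The 45/25/20/10 proportional-odds row uses 12,000 simulated trials and the others 3,000, with a standard error of at most √(0.25/3000) = 0.9 points for each power. The gain is about 15 to 17 points under proportional odds and 10 to 14 with the mix unchanged. With no true difference the rejection rates at 47 per arm are 4.5% (Fisher) and 4.8% (Mann-Whitney), so the gain does not come from a looser test.

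**One table as illustration.** Take counts close to the planned effect at 47 per arm: tramadol 21/12/9/5 and PNB 33/8/4/2. Fisher p = 0.085; Mann-Whitney p = 0.010. Move the same counts to other grade columns (12/21/5/9 vs 8/33/2/4): Fisher is still 0.085, while Mann-Whitney becomes 0.54. Only the second test responds to which grade the patients are in.

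**Patterns that are not a consistent shift, Fisher / Mann-Whitney, %**

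| Tramadol vs PNB grades (%) | 37 per arm | 47 per arm |
|---|---|---|
| 45/15/25/15 vs 45/40/10/5 (same incidence, milder) | 69 / 20 | 83 / 24 |
| 45/20/20/15 vs 70/25/4/1 (strong fall in the higher grades) | 83 / 81 | 93 / 89 |
| 45/25/20/10 vs 70/5/15/10 (mainly mild cases fall) | 62 / 37 | 76 / 46 |

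**The case against.** The strongest objection is that the power gain is not a property of the plan. The article gives no grade split and no shift pattern, and proportional odds is the setting that favours a rank test. In all three patterns of the last table PNB is no worse at any cut-point, yet Fisher's test has more power. The first of them, moderate and severe cases becoming mild at equal incidence, is a pattern where severity tells the reader something the primary outcome cannot. This stands. A reader might infer that the stated test costs a fixed 17 points, and the documents do not support that.

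A reader might also infer that the test is invalid or inflates false positives. It does not; it keeps its 5% level.

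It can be argued that the two-arm by four-grade table is itself inferred, and that Fisher's test on grade 2 or more would be directional. The article states no such cut, so this remains open. It would not recover the loss under proportional odds: for 30% vs 13.1% in grades 2 and 3 at 47 per arm (the 45/25/20/10 split), Fisher's power is about 42%.

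Lack of direction or of an effect size is a weak complaint. The grade table shows direction for either test, and Mann-Whitney alone gives no effect size either.

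Finally, because grades are taken repeatedly to 6 h and grades 2 and 3 lead to rescue tramadol, a reader might infer that severity will be tested visit by visit on grades already altered by rescue. The article states no such analysis, so this is not a fault in it.

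**Conclusion.** The point holds as a matter of efficiency and fit. An ordered grade with a directional question is assigned a test that, on the natural reading, ignores the order, although the same paragraph uses a rank test elsewhere. With the planned 55% vs 30%, assumed grade splits and two-sided tests at 5%, an order-using test gains about 10 to 17 points of power at 37 to 47 per arm when the benefit is consistent across grades. The sign can reverse for other patterns, so the size is conditional. The ordinal test is still the better default, because it addresses whether severity is lower. The matter affects the leading secondary outcome and not the primary one. It deserves correction but does not threaten the trial's validity.

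**What to change.** Replace the Fisher sentence under Statistical analysis with, for example: severity will be compared using one grade per patient (such as the worst grade over 0 to 6 h) by the Mann-Whitney U test, or by a proportional-odds model reporting a common odds ratio with 95% CI. Keep the grade-by-arm table as description, so that a change concentrated in particular grades remains visible.

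The cost is one sentence. It needs no new data, patients or change in care, and the Mann-Whitney test is already in the plan. Trial status says recruitment had not begun, so the change can be made before any outcome is seen. The one downside is lower power than Fisher's test if the effect is not a consistent shift.

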## Discussion

PNB, a local anesthetic technique, has been applied widely in patients undergoing perineal and vaginal surgery [13–15], for relief of pudendal neuralgia [16], and for treatment of detrusor-sphincter dyssynergia and external urethral sphincter hypertonicity in patients with spinal cord injury [19, 20]. In addition, a combination of pudendal and periprostatic nerve block has been reported to improve pain reduction during transperineal prostate biopsy compared with periprostatic anesthesia only [21]. On the basis of findings reported in the literature and the neural anatomy that sensation of the bladder triangle and urethra provided by the pudendal nerve derived from sacral nerves S2–S4, we hypothesize that PNB could reduce the incidence of CRBD as well as side effects due to less nerve-related side effects associated with nerve block than intravenous systemic administration of antimuscarinic agents.

As a weak opioid with a potent antimuscarinic effect, tramadol is commonly used for postoperative pain relief and chronic pain management [22, 23], and it is reported to halve the incidence of postoperative CRBD [6] and is administered to patients with severe CRBD as a rescue treatment [9]. Therefore, we chose intravenous tramadol administration as the control and will test the superiority of PNB with 0.33 % ropivacaine to tramadol 1.5 mg/kg in CRBD prevention. On the basis of a previous study [9], intravenous tramadol 1.5 mg/kg will be given to the patients with moderate to severe CRBD as a rescue treatment to relieve their bladder discomfort.

During the execution of the PNB trial, all eligible patients will receive the allocated intervention while under general anesthesia, and the research nurses responsible for follow-up and the statistician will not be aware of to which group the patient or data belongs, so the patients, the research nurses, and the statistician will be blind to the group allocation. A 16-French Foley catheter will be inserted into the patients in the present study to test the effects of CRBD prevention because this diameter of the Foley catheter is superior to the 18-French diameter and has been reported to be an independent predictor responsible for moderate or severe CRBD [1]. Sterilized liquid paraffin will be applied for catheterization for prevention against urethral mucosal injury, but local anesthetics will not be spread onto the surface of catheter, to minimize other confounding factors related to CRBD. Furthermore, although we will test the superiority of PNB with ropivacaine to intravenous tramadol in CRBD prevention, we do not aim to deny the beneficial effects of antimuscarinic agents to relieve CRBD. Instead, we will use tramadol as a rescue treatment to reduce bladder discomfort in the PACU.

There are several limitations of this trial. First, with regard to the study design, because of different routes of administration (nerve block vs. intravenous), the investigator and responsible physicians will not be blind to group allocation. Second, PNB will be performed with the patient in lithotomy position in current clinical practice, so we will choose patients undergoing prostate surgery placed in the lithotomy position. Therefore, a limitation exists in the application of PNB to patients undergoing other operations in the supine, prone, or other position, and other routes of PNB should be explored in the next step. Third, for patients undergoing medical procedures requiring urinary catheterization without any surgical intervention, the risks and benefits of PNB should be balanced, and this aspect will not be discussed in this study. In addition, CRBD is a very subjective feeling, and it can be defined only semiquantitatively on the basis of the patient’s own complaint and the physician’s judgment. That is why the incidence of CRBD varies in different articles [1, 3], and we will try our best to get an accurate measurement of CRBD by careful follow-up.

In summary, this trial is designed to find an optimal clinical practice for CRBD reduction by performing a superiority test for the PNB with 0.33 % ropivacaine compared with intravenous tramadol 1.5 mg/kg.

## Trial status

The study is not yet recruiting as of the date of publication.

## Abbreviations

CONSORT: Consolidated Standards of Reporting Trials
CRBD: Catheter-related bladder discomfort
PNB: Pudendal nerve block
NRS: Numeric Rating Scale
PACU: Postanesthesia care unit
SPIRIT: Standard Protocol Items: Recommendations for Interventional Trials
